## Abstract

**Background:**

The control of the lower urinary tract is a complex, multilevel process involving both the peripheral and central nervous system. Due to lesions of the neuraxis, most spinal cord injury patients suffer from neurogenic lower urinary tract dysfunction, which may jeopardise upper urinary tract function and has a negative impact on health-related quality of life. However, the alterations to the nervous system following spinal cord injury causing neurogenic lower urinary tract dysfunction and potential effects of treatments such as intradetrusor onabotulinumtoxinA injections on lower urinary tract control are poorly understood.

**Methods/Design:**

This is a prospective structural and functional magnetic resonance imaging study investigating the supraspinal lower urinary tract control in healthy subjects and spinal cord injury patients undergoing intradetrusor onabotulinumtoxinA injections for treating neurogenic detrusor overactivity.

Neuroimaging data will include structural magnetic resonance imaging (T1-weighted imaging and diffusion tensor imaging) as well as functional, i.e. blood oxygen level-dependent sensitive magnetic resonance imaging using a 3 T magnetic resonance scanner. The functional magnetic resonance imaging will be performed simultaneously to three different bladder stimulation paradigms using an automated magnetic resonance compatible and synchronised pump system.

All subjects will undergo two consecutive and identical magnetic resonance imaging measurements. Healthy subjects will not undergo any intervention between measurements but spinal cord injury patients will receive intradetrusor onabotulinumtoxinA injections for treating neurogenic detrusor overactivity.

Parameters of the clinical assessment including bladder diary, urinalysis, medical history, neuro-urological examination, urodynamic investigation as well as standardised questionnaires regarding lower urinary tract function and quality of life will serve as co-variates in the magnetic resonance imaging analysis.

**Discussion:**

This study will identify structural and functional alterations in supraspinal networks of lower urinary tract control in spinal cord injury patients with neurogenic detrusor overactivity compared to healthy controls. Post-treatment magnetic resonance imaging measurements in spinal cord injury patients will provide further insights into the mechanism of action of treatments such as intradetrusor onabotulinumtoxinA injections and the effect on supraspinal lower urinary tract control.

**Trial registration:**

ClinicalTrials.gov NCT01768910.

## Background

Spinal cord injury (SCI) is a devastating event with far-reaching consequences for the individual’s health and the economic and social future. In the past, renal failure due to neurogenic lower urinary tract dysfunction (NLUTD) was a leading cause of death after SCI [1]. Furthermore, NLUTD has a highly negative impact on patients’ quality of life (QoL). Acute SCI initially causes “spinal shock”, characterised by an acontractile/hypocontractile detrusor and urinary retention, which in case of a suprasacral lesion (today the vast majority of SCI) is followed by development of detrusor overactivity mostly combined with detrusor sphincter dyssynergia [2]. Antimuscarinics are the pharmacological first-line treatment for detrusor overactivity although the effectiveness is limited [3]. In addition, many patients discontinue antimuscarinics due to bothersome side-effects [4]. Thus, intradetrusor onabotulinumtoxinA injections have become an established, highly effective, minimally invasive, and generally well-tolerated therapy for refractory detrusor overactivity [5] to improve patients’ health and QoL [6]. Despite the popularity of intradetrusor onabotulinumtoxinA injections, the exact mechanisms of action remain to be elucidated. Nevertheless, it seems highly probable that, in addition to a direct efferent effect by blocking the presynaptic release of acetylcholine from the parasympathetic innervation resulting in temporary chemodenervation of the detrusor, onabotulinumtoxinA also modulates afferent pathways [7]. It is, however, not known whether this treatment can normalise alterations in supraspinal areas and whether supraspinal modulation correlates with clinical improvements.

The control of the lower urinary tract (LUT) is a complex, multilevel process that involves both the peripheral and central nervous system but the exact mechanisms involved in humans are still incompletely understood [8]. Neuroimaging studies over the last decade have consistently pointed to a complex supraspinal network that controls LUT function [9]. These studies tremendously increased our understanding of how human LUT function is coordinated and how it can be affected by neurological disorders. Recent neuroimaging studies demonstrated reorganisation of supraspinal activity in response to LUT stimulation tasks in patients with disorders such as Parkinson’s disease [10-12] and SCI [13] as compared to healthy controls, which might represent the neural correlate of their NLUTD.

Cortical and sub-cortical (for example, brainstem) brain regions are essential for voluntary LUT control [9,14,15]. Investigation of the supraspinal regions with high-resolution imaging techniques, for example, structural magnetic resonance imaging (MRI) and functional MRI (fMRI), can significantly increase our knowledge on the effects of supraspinal lesions and alterations related to NLUTD [9,16]. Although diffusion tensor imaging (DTI) [17] is popular in other fields in neuroscience, it has only been applied in the context of supraspinal LUT control in one prospective study [18] in patients with non-neurogenic LUT symptoms.

In this study, we will first identify supraspinal areas associated with LUT control in SCI patients with neurogenic detrusor overactivity and healthy controls. Subsequently, we will investigate the effects of intradetrusor onabotulinumtoxinA injections on supraspinal areas. Task-related blood oxygen level-dependent (BOLD) fMRI will be used along structural MRI (T1-weighted and DTI). Moreover, we will examine volumetric parameters (for example, grey and white matter concentration) by voxel- (VBM) [19] and tensor-based morphometry (TBM) [20], structural integrity and connectivity of white matter tracts (DTI) as well as structural (SC) and functional connectivity (FC).

This unique and detailed multimodal imaging and clinical approach will distinguish the different structural and functional processing units involved during supraspinal LUT control and will identify dysfunctional neuronal components in SCI patients responsible for neurogenic detrusor overactivity.

For a test-retest validation, we will additionally investigate the reliability [21] of BOLD signals in task-related fMRI in healthy controls by the intra-class correlation coefficient (ICC) for absolute or consistent agreement of participants activations over two visits.

## Methods/Design

### Study design

This prospective research study will be conducted at the University of Zürich, Zürich, Switzerland in cooperation with our partner, the institute of Neuro-Radiology, University of Zürich, University Hospital Zürich, Zürich, Switzerland.

### Study location

The study has two study locations, that is, the department of Neuro-Urology, Spinal Cord Injury Centre & Research, University of Zürich, Balgrist University Hospital, Zürich, Switzerland (first and third visit, see below) and the MR-Centre, University Hospital Zürich, Zürich, Switzerland (second and third visit, see below).

### Study population and recruitment

In line with the inclusion and exclusion criteria (Table 1), we will investigate SCI patients with neurogenic detrusor overactivity and healthy controls with an unimpaired LUT function. Participants of both groups will be similar according to age and gender.

**Table 1 T1:** Inclusion and exclusion criteria for all participants

**Groups**	**Inclusion criteria**	**Exclusion criteria**
All participants	• MR suitability	• Pregnancy or breast feeding
	• Written informed consent	• Any anatomical anomaly of LUT/genitalia
		• Any LUT malignancy
		• Claustrophobia
SCI patients	• Age limit: > 18 years	• Symptomatic UTI
	• Neurogenic detrusor overactivity	
	• Refractory to antimuscarinic treatment	
	• Scheduled for intradetrusor onabotulinumtoxinA injections	
Healthy controls	• Age limits: > 18 years	• Impaired LUT function
	• Unimpaired LUT function	• Any LUTS (3-day bladder diary)
	• No LUTS (3-day bladder diary)	• Any number of episodes of urinary urgency/week
	• No episode of urinary urgency/week	• Urinary frequency > 8/24 h
	• Urinary frequency < 8/24 h	• Any craniocerebral injury or surgery
		• Any permanent ferromagnetic implant
		• Any previous surgery of LUT/genitalia
		• UTI
		• PVR > 150 mL

LUT = lower urinary tract, LUTS = lower urinary tract symptoms, MR = magnetic resonance, PVR = post void residual, SCI = spinal cord injury, UTI = urinary tract infection.

20–24 SCI patients with neurogenic detrusor overactivity refractory to antimuscarinics and scheduled for study independent intradetrusor onabotulinumtoxinA injections and 12–24 healthy controls will be recruited.

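### Table 1 excludes no co-existing brain disease in SCI patients, so the patient-control differences in Primary A–C can be partly confounded by such disease, probably to a modest degree

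*Protocol article*

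**What the plan says.** All references are to the protocol article.

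- **Study population and recruitment:** "we will investigate SCI patients with neurogenic detrusor overactivity and healthy controls with an unimpaired LUT function". The two groups are to be similar in age and gender. Planned numbers are "20–24 SCI patients with neurogenic detrusor overactivity refractory to antimuscarinics" and "12–24 healthy controls will be recruited".
- **Table 1, all participants:** the exclusions are pregnancy or breast feeding, "Any anatomical anomaly of LUT/genitalia", malignancy of the lower urinary tract (LUT), and claustrophobia.
- **Table 1, SCI patients:** the single specific exclusion is "Symptomatic UTI".
- **Table 1, healthy controls:** the exclusions include "Any craniocerebral injury or surgery", "Impaired LUT function", any LUT symptoms and any urgency.
- **Background:** imaging studies have shown "reorganisation of supraspinal activity in response to LUT stimulation tasks in patients with disorders such as" Parkinson's disease, and also in SCI. The study is expected to find the brain components in SCI patients that account for their detrusor overactivity.
- **Study outcome measures:** Primary A and B compare SCI patients with controls. Primary C covers connectivity in both groups.
- **Interventions, Screening (Visit 1):** medical history is one basis for eligibility. No neurological criterion is tied to it.

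**The concern.** Every primary outcome is measured in the brain. The protocol names a second class of disease that changes one of these measures, task-related activity during bladder stimulation, yet sets no criterion that keeps such disease out of the patient group. Similarity in age and gender does not remove it.

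At stake is attribution. A patient with SCI and a separate brain disease contributes both conditions to the patient mean, and the patient-control contrast cannot separate them. This is bias as well as extra variance. Its direction relative to the SCI effect is unknown, so it could enlarge or mask a true difference.

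**Working it through.** **1. Reading the criteria against the reasoning**

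| Criterion | SCI patients | Controls |
|---|---|---|
| Neurological or brain disease named as an exclusion | No | No |
| Head injury or cranial surgery excluded | No | Yes |
| Bladder dysfunction or symptoms excluded | No (detrusor overactivity is required) | Yes |
| Described as healthy | No | Yes |

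Table 1 is presented as the inclusion and exclusion criteria for all participants. Followed as written, it admits an SCI patient with, for example, Parkinson's disease. For controls, three other rules make this unlikely.

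**2. Shift in the patient mean**

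The article states no effect size, alpha, power or sample-size derivation, so there is no trial figure to reproduce. What follows is an illustration.

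Inputs from the protocol: patient group n1 = 20 to 24, control group n2 = 12 to 24. Assumed: k affected patients, each shifted by d SD on one region-of-interest measure. The documents give neither k nor d.

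Shift = k × d / n1. For example, 1 × 2 / 20 = 0.10 SD and 2 × 2 / 20 = 0.20 SD.

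**3. False-positive rate for one measure with no true SCI effect**

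Two-sided 5% z-test, SE = √(1/n1 + 1/n2):

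- 20 vs 12: √(1/20 + 1/12) = 0.365
- 24 vs 24: √(1/24 + 1/24) = 0.289

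Rate = P(Z > 1.96 − shift/SE) + P(Z < −1.96 − shift/SE).

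| k | d (SD) | Shift, 20 vs 12 | Rate | Shift, 24 vs 24 | Rate |
|---|---|---|---|---|---|
| 1 | 1 | 0.05 | 5.2% | 0.04 | 5.2% |
| 1 | 2 | 0.10 | 5.9% | 0.08 | 6.0% |
| 2 | 1 | 0.10 | 5.9% | 0.08 | 6.0% |
| 2 | 2 | 0.20 | 8.5% | 0.17 | 8.9% |
| 4 | 2 | 0.40 | 19.5% | 0.33 | 21.1% |

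**4. Comparison with what the study can detect**

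Assuming a two-sample t-test with 80% power and two-sided 5%, the detectable difference is about 1.06 SD at 20 vs 12 and 0.83 SD at 24 vs 24. With one or two affected patients and d = 2, the shift is 0.10/1.06 = 9% or 0.20/1.06 = 19% of that at 20 vs 12, and 0.083/0.83 = 10% or 0.167/0.83 = 20% at 24 vs 24.

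**The case against.** **The control group is largely protected.** A reader might infer that neither group is screened and that controls count as healthy on bladder function alone. The text does not support this. Controls are described as healthy, must be free of LUT symptoms and urgency, and are excluded for "Any craniocerebral injury or surgery", which is a brain criterion. The Background ties the reported reorganisation to patients with LUT dysfunction, so it does not show that symptom-free controls would be affected. Brain disease is not named for controls either, but the remaining risk there is small. This objection stands.

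**The effect is small under plausible inputs.** With one or two of 20 patients affected, the false-positive rate for one measure stays between 5% and 9%. Reaching about 20% takes four patients, each shifted by 2 SD. This also stands. It rules out the stronger reading that A to C would measure another disease in place of SCI.

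**The overactivity has an evident cause.** The Background says that suprasacral SCI, the large majority of cases, is usually followed by detrusor overactivity, and patients come through a spinal cord injury centre. A suggestion that another disease produced the overactivity would be conjecture. The point does not need it: a co-existing disease can alter the brain measures whatever caused the overactivity.

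**A fuller protocol may say more.** How the medical history is applied could be detailed elsewhere. However, Table 1 sets out the criteria for each group, and the patient list contains nothing neurological to apply.

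**Conclusion.** The point holds for the patient group. Table 1 leaves open a source of confounding that the protocol's own Background identifies, and the patient-control differences in Primary A to C can partly reflect it. The size is unknown and probably modest: 0.10 to 0.20 SD if one or two of 20 patients are affected and each is shifted by an assumed 2 SD, less if the shift is smaller.

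Three limits apply:

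- Primary D is a within-patient change, so a stable co-existing disease affects it less.
- A reader might also infer that such patients would dominate the Secondary B correlations. Nothing in the documents or the calculations above establishes that.
- The exclusion of head injury and cranial surgery in controls only is a related imbalance. It concerns trauma and surgery, and this point does not rest on it.

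**What to change.** Add one exclusion to Table 1 under all participants: *any known neurological disease affecting the brain other than the spinal cord injury*. Check it from the medical history already taken at Visit 1. Placing it under all participants applies the same rule to both groups and makes explicit what the healthy label implies for controls.

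The article reports that recruitment is under way. For patients already enrolled, record any such disease from the history and repeat Primary A to C without the affected participants as a sensitivity analysis.

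The cost is one eligibility line, one repeated analysis and the loss of a few candidates. No additional examination is needed.

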### Study outcome measures

#### Primary

(A) Task-related BOLD signal intensity in supraspinal regions of interest (ROI) in SCI patients with neurogenic detrusor overactivity compared to healthy controls.

(B) Supraspinal morphometry of ROIs in SCI patients with neurogenic detrusor overactivity compared to healthy controls.

(C) SC and FC between ROIs of the supraspinal LUT controlling circuitries in SCI patients with neurogenic detrusor overactivity and healthy controls.

(D) Changes of task-related BOLD signal intensity, SC and FC between ROIs in SCI patients with neurogenic detrusor overactivity before and after study independent intradetrusor onabotulinumtoxinA injections.

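### Craniocerebral injury or surgery excludes healthy controls but not spinal cord injury patients, so the primary group comparisons A to C can confound brain injury with spinal cord injury and bladder dysfunction

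*Protocol article*

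**What the plan says.** Under Study population and recruitment, Table 1 has three rows.

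- **All participants:** the exclusions are pregnancy or breast feeding, "Any anatomical anomaly of LUT/genitalia", malignancy of the lower urinary tract, and claustrophobia. One inclusion criterion is "MR suitability", which is not defined further.
- **SCI patients:** the only exclusion is "Symptomatic UTI".
- **Healthy controls:** the exclusions include "Any craniocerebral injury or surgery".

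On comparability, the same section says: "Participants of both groups will be similar according to age and gender". It names no other matching factor.

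Three of the four primary outcomes involve both groups. Outcome A sets the strength of the task-related signal in chosen brain regions of patients against that of controls. Outcome B does the same for brain structure, and its wording shows the form of the comparison: "Supraspinal morphometry of ROIs in SCI patients with neurogenic detrusor overactivity compared to healthy controls". The third of them, outcome C, covers how these regions are connected, structurally and functionally, in both groups.

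Outcome D is a change within patients, before and after treatment.

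The Abstract (Methods/Design) includes medical history among the clinical parameters that will act as covariates in the imaging analysis. The covariates listed under secondary outcome B are bladder diary, urodynamics and desire to void. Head injury is named in neither place.

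**The concern.** The protocol treats a history of head injury or brain surgery as a reason to keep a person out of the control group of a brain-imaging study, but applies that rule to one side of the comparison only. Such a history can change grey matter, white matter tracts and task-related signal for reasons unrelated to the cord or the bladder. By design it is absent among controls and permitted among patients.

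The Background says that the study will identify the brain components responsible for neurogenic detrusor overactivity. If some enrolled patients have had a brain injury, part of a difference in A, B or C may come from that injury. Such a bias does not shrink as the sample grows. For a given bias, a larger sample makes a false finding more likely, because the standard error falls while the bias stays.

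This is a stated eligibility rule, not a detail left to a fuller document. A later analysis plan could restrict or adjust the analysis, but it cannot change who was enrolled.

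**Working it through.** **Reading the criteria.** The plan gives no figure to reproduce. The first check is whether any other text extends the criterion to patients.

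1. The patient row and the all-participant row of Table 1 do not mention the head or brain.
2. "MR suitability" applies to everyone, but the article does not say that it covers past brain injury.
3. Similarity of the groups is promised for age and gender only.
4. Screening (Visit 1) uses medical history to judge eligibility, but only against the listed criteria.

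So a patient with such a history meets the criteria as written.

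**Inputs for the size.**

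- From the document: 20-24 patients and 12-24 controls. The two cases used are 20 vs 12 and 24 vs 24.
- Assumed, because the document gives none: two-sided alpha 0.05 for a single regional test; SD 1; a share p of 10-40% of patients with prior head injury or brain surgery; a shift d of 0.8-1.0 SD in the same measure and direction; no true effect of SCI or bladder dysfunction.

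**Bias.** Spurious group difference = p × d.

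- Low: 0.10 × 0.8 = 0.08 SD
- Middle: 0.25 × 0.8 = 0.20 SD
- High: 0.40 × 1.0 = 0.40 SD

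**False-positive rate.** Two-sample t-test, noncentrality = bias / √(1/n₁ + 1/n₂).

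- 20 vs 12: √(1/20 + 1/12) = 0.365, 30 degrees of freedom
- 24 vs 24: √(1/24 + 1/24) = 0.289, 46 degrees of freedom

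| Bias (SD) | 20 vs 12 | 24 vs 24 |
|---|---|---|
| 0.08 | 0.055 | 0.058 |
| 0.20 | 0.083 | 0.104 |
| 0.40 | 0.185 | 0.274 |

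**Check on the variance.** A patient group in which only some members are shifted has variance 1 + p(1 − p)d², not 1. With that variance and a normal approximation, the 0.40 SD case gives 0.183 (20 vs 12) and 0.258 (24 vs 24), and the 0.08 SD case gives 0.055 and 0.059. The picture does not change.

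**After the change.** With the criterion in both groups, p = 0 in each. The bias from this source is 0, and the rate returns to the nominal 5%.

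**Patients lost from A to C under the same assumed share.** 0.10 × 20 = 2 to 0.40 × 20 = 8 of 20; 0.10 × 24 = 2.4 to 0.40 × 24 = 9.6, so about 2 to 10 of 24.

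**The case against.** A reader might go further and infer that the effect of head injury cannot be adjusted for at all, because no control has one. That does not follow. There are three kinds of participant: controls, patients without head injury and patients with it. An indicator for head injury can be estimated from the variation among patients, and the contrast of unaffected patients with controls is then identified. The Abstract also names medical history as a covariate. What remains is weaker but real: head injury is not named, the more specific covariate list under secondary outcome B omits medical history, and the effect would be estimated from 20-24 patients alone, so imprecisely.

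A second tempting reading is that A to C are in fact confounded. The documents do not show this. They give no prevalence, and Table 1 does not require the cord injury to be traumatic. One accident that injures both head and cord is possible, but the article does not describe it. At the low end of the assumed range the effect is negligible, and the calculation further assumes that every injury shifts the same measure in the same direction. Only the statement that the comparisons can be confounded is supported.

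Outcome C says 'and healthy controls' where A and B say 'compared to'. This matters little, since the Discussion states a comparison with controls as the aim.

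**Conclusion.** The concern holds in conditional form. The criterion is one-sided on the face of Table 1 and nothing else in the article extends it to patients, so A to C can attribute effects of brain injury to spinal cord injury and bladder dysfunction. That reading of the criteria is firm; the size is not. Under the assumed 10-40% share and 0.8-1.0 SD shift, a 5% test rejects falsely about 6% of the time at the low end, and 19% (20 vs 12) or 27% (24 vs 24) at the high end. A range that runs from negligible to material supports a change that should be made, not a finding that the study is invalid. The within-patient contrast in D is not affected in the same way.

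**What to change.** For future enrolment, move the criterion from the healthy-control row of Table 1 to the exclusions for all participants. The article reports that the trial is recruiting, so the change can still take effect.

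For patients already enrolled, identify such a history from the medical history taken at screening, by a definition written down in advance and applied by someone blind to the imaging results. Appearance on the T1-weighted scan should not be used: it is structural imaging of the kind on which the morphometry in outcome B rests, so removing patients on that basis risks selecting on the outcome. Then either leave these patients out of A to C, or keep them and report a prespecified sensitivity analysis of A to C without them. They may stay in outcome D.

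The cost is a one-line amendment, a sentence defining the analysis set, fewer eligible patients, and a smaller set for A to C: 2 to 8 of 20, or about 2 to 10 of 24, if the assumed share is right. At the upper end that loss is substantial. The sensitivity analysis is the less costly choice for those already enrolled, but it leaves the main analysis exposed.
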